### Cardiac reserve

#### Exercise cardiac magnetic resonance imaging

The biventricular response to supine cycle exercise will be evaluated using a real-time CMR protocol that has been detailed previously and validated against invasive measures [64]. In brief, ungated real-time steady-state free-precession (SSFP) cine MR imaging will be conducted using a Siemens MAGNETOM Prisma 3.0 T CMR with a five-element phased array coil. Forty to 75 consecutive frames will be acquired at a temporal resolution of 36–38 ms for each ~ 10–18 adjoining 8 mm image slices in both the short and long-axis planes, encapsulating both ventricles. Imaging parameters will be as follows: field of view, ~ 320 × 260 mm; matrix, 128 × 128; flip angle, 50°; SENSE factor, 2 (Cartesian k-space undersampling); repetition time, 1.8 for ms; echo time, 0.9 ms; and reconstructed voxel size, 2.3 × 2.3 × 8 mm. Cardiac images will be obtained at rest, and whilst cycling on an MR compatible supine cycle ergometer (MR Ergometer Pedal, Lode, Groningen, the Netherlands) at workloads corresponding to 20%, 40%, and 60% of the maximal power output achieved during upright CPET as this approximates low, moderate, and maximal exercise capacity in the supine position [64, 65]. Each workload will be maintained for 1.5–3 min (comprising ~ 30 s to achieve a physiological steady state, and 1–2.5 min for image acquisition), with the imaging duration decreasing with each increasing intensity level.

Real-time cine images will be analysed offline in a software developed in-house (Right Volume Software Program, Leuven, Belgium). Images will be retrospectively synchronised to cardiac and respiratory cycles to ensure endocardial contouring is performed at end-expiration for consistency. The left and right ventricular endocardial contours will be manually traced in the short-axis plane, and the transection points with the long-axis plane will be marked, to allow cross-referencing to the atrioventricular valve plane when defining endocardial contours. Ventricular volumes will be quantified at rest and at each increasing exercise intensity level (low, moderate, and high) via the summation of disc method (papillary muscles and trabeculations included in the blood pool). Stroke volume index (SVI) will be obtained by subtracting end-systolic volume (RVESV + LVESV/2) from end-diastolic volume (RVEDV + LVEDV/2) indexed to body surface area (BSA). Cardiac index (CI) will be calculated by multiplying SV (RVSV + LVSV/2) by HR indexed to BSA. Left and right ventricular ejection fractions (LVEF, RVEF) will be calculated as the ratio of EDV to SV, multiplied by 100 to be reported as a percentage. Cardiac (CI, SVI, HR) and contractile (LVEF, RVEF) reserve will be defined as the heart's ability to augment its function in response to maximal exercise (peak exercise value – rest value). Using this novel technique of cardiac volume analysis, our laboratory has demonstrated exceptional inter-study and inter-observer reproducibility (inter-study cardiac output: *R* = 0.98; inter-observer left- and right-ventricular SV: *R* = 0.98 and *R* = 0.97, respectively) [64].

### Resting cardiac structure and function

#### Resting echocardiography

A comprehensive resting echocardiogram assessment will be used to characterise cardiac structure and function (Vivid E95, GE Healthcare, Horten, Norway). This is the current standard of clinical care and will include Doppler and 3-dimensional volumetric acquisitions and torsion, global longitudinal strain (GLS), and strain rate measures. Left-ventricular ejection fraction (LVEF) will be quantified and used to assess left ventricular systolic function according to standard recommendations. All images acquired will be analysed using offline analysis software (Echopac V13.0.00, GE, Norway).

### Cardiac magnetic resonance imaging

Using an identical protocol as described previously [66], myocardial tissue characterisation and cardiac mass will be assessed using non-contrast T1 mapping and breath-hold SSFP sequences, respectively.

### Vascular function

#### Blood pressure

Supine systolic- and diastolic blood pressure will be measured from the brachial artery using an oscillometric blood pressure monitor (OMRON HEM-907, OMRON Corporation, Tokyo, Japan). Measurements will be taken after ≥ 10 min rest in the supine position and the average of three measurements, taken ≥ 3 min apart, will be used for analysis. Where one of three measurements is substantially different from the other two, a fourth measurement will be taken.

#### Cardiac magnetic resonance imaging

Central (aortic) compliance will be assessed using ECG-gated resting CMR cine-imaging conducted prior to the ExCMR, as a measure of vascular function. Transverse images of the ascending aorta will be taken just above the sinotubular junction. Cine images will be analysed for changes in 2-dimensional area across the cardiac cycle that can be incorporated with SV (calculated from breath-hold SSFP images) and pulse pressure (obtained from brachial blood pressure measured by an automated cuff) to calculate aortic distensibility and compliance in line with previously validated methods [67].

### Anthropometrics, body composition and bone mineral density

#### Anthropometry

Body height and weight will be measured using a fixed stadiometer (SECA, Hamburg, Germany) and portable scales (Coverall Medical Technologies, Victoria, Australia), and used to calculate body mass index and BSA.

#### Dual energy X-ray absorptiometry

Total body and regional lean mass, fat mass and percentage body fat will be measured via a total body dual energy X-ray absorptiometry (DXA) scan (GE Lunar iDXA, GE Healthcare, Little Chalfont, United Kingdom). DXA has the capacity to efficiently and non-invasively measure total body composition with excellent precision and accuracy (coefficient of variation < 1%) [68, 69]. Scans will be manually analysed using enCore analysis software (version 14.10.022) in line with standardised procedures.

#### Magnetic resonance imaging

Quadricep muscle cross-sectional area and intramuscular fat content will be assessed by two-point Dixon-based MRI (Siemans Prisma 3 T MRI). The two-point Dixon method has been validated as an accurate and reproducible (CV = 0.6%) measurement of muscle-fat content. MRI scans of the right thigh will be acquired in the supine position, from the superior patella to the greater trochanter. Images will be analysed using openly available ImageJ software (ImageJ2 v1.52d) to manually outline the regions of interest (rectus femoris, vastus intermedius, vastus medialis and vastus lateralis). Muscle volume will be calculated from the summation of disks method by multiplying the sum of the combined regions of interest by the inter-slice distance. Fat fraction will be calculated from the ratio between the fat and combined fat and water signal intensities for the regions of interest.

### Biochemistry

Fasting blood samples will be collected. Analysis of these samples will be performed by the Alfred Hospital Pathology Laboratory. The assessments performed will include a full blood examination, liver function tests, and serum chemistry. In addition, markers of myocardial injury (cTn-I) and myocardial stress (BNP), glycaemic control (fasting glucose, HbA1C), and lipid profiles (total-, LDL- and HDL cholesterol and triglycerides) will be collected.

### Physical function

Physical function testing will be performed as per standardised guidelines and include the six-minute walk test, hand-grip strength test and the short physical performance battery (SPPB) encompassing the five times sit-to-stand test, 4 m usual gait speed test, and static balance measured by side-by-side, semi-tandem and tandem stand balance tests [70, 71]. SPPB scores range from zero (high frailty) to 12 (low frailty) possible points. A score of ≥ 10 will be considered ‘normal’, while scores of 7–9, 4–6 and 0–3 will indicate mild, moderate and severe limitations in lower extremity function, respectively [72].

### Quality of life, fatigue, anxiety and depression

Quality of life will be assessed using the Functional Assessment of Cancer Therapy with Bone Marrow Transplant (FACT-BMT)—a 50 item subscale specifically designed to assess multidimensional quality of life in bone marrow transplant recipients. Fatigue will be assessed using the 13 item Functional Assessment of Chronic Illness Therapy – Fatigue subscale (FACIT-Fatigue), while anxiety and depression will be assessed using the Hospital Anxiety and Depression Scale (HADS). All questionnaires have been validated in cancer populations.

### Diet, physical activity, sedentary time, and sleep

#### 3 day food diary

Habitual dietary intake will be assessed using a 3 day diet record completed using the Easy Diet Diary smartphone application. Participants will be required to record the type and quantity of food and beverage consumed over a 24 h period for two weekdays and one weekend day. Data entered into Easy Diet Diary will be exported into FoodWorks 10 Professional (Xyris, Australia), and average energy intake and macronutrient composition will be quantified.

#### 7 day accelerometry and inclinometry

Habitual physical activity and sedentary time will be assessed over 7 days utilising a hip-worn accelerometer (Actigraph GT3X +) and thigh-worn inclinometer (ActivPAL3). This wear-time aligns with recommendation for objective physical activity assessment in cancer cohorts. Inclinometer data will be exported using ActivPAL3™ software (v.8.10.9.46, PAL Technology, UK) and analysed for time spent sedentary (h/day), in prolonged sitting ≥ 60 min (h/day), standing (h/day), and stepping (h/day). Actigraph data will be exported using ActiLife software (ActiGraph, V6.13) and used to assess energy expenditure (metabolic equivalent of task [MET] min/day) and daily activity levels based on Freedson cut-points for sedentary, light, moderate and vigorous physical activity levels [73].

#### 7 day sleep log

Sleep quantity and quality will be assessed using a 7 day sleep log. Participants will document the time of sleep onset and cessation, the frequency and length of any awakenings and rate their sleep quality on a 5-point scale from very poor to very good.

#### Fitabase

Additional information regarding habitual physical activity, sedentary behaviour and sleep will be collected via Fitbit devices and collated on Fitabase (a cloud-based data aggregation platform). Specifically, Fitbit devices will be worn continuously for the entirety of the study (~ 4 months) to allow comprehensive longitudinal insight into the physical activity (e.g., number of steps [steps/day], as well time spent in light, moderate and high intensity activity [min/day]), sedentary behaviour (e.g., time spent sitting [min/day], time spent in prolonged sitting [≥ 60 min/day], and sleep quality and quantity (time spent awake, and in light, REM, or deep sleep [min/day]) of participants.

### Transplant outcomes

Additional transplant-related outcomes will be recorded from Alfred Health patient medical records including the duration of hospital stay during the transplant procedure, time to engraftment, GVHD prophylaxis, development and severity, steroid use, and other relevant medications and/or complications (including rehospitalisation).

### Semi-structured interview (Ex + SED group only)

A semi-structured interview with an interpretive phenomenological framework will be conducted to evaluate the lived experiences of those who participated in the ALLO-Active Ex + SED Program. The interview will be held in a private room, audio recorded, and follow a semi-structured interview guide designed to extract information relating to barriers, facilitators, positives and negatives, and overall experience in the ALLO-Active Ex + SED Program.

### Ex + SED adherence and attendance

Attendance and adherence to the prescribed structured exercise sessions, and exercise dose within each exercise session will be manually documented into a REDCap (REDCap, Vanderbilt University, Nashville, USA) database. Attendance will be calculated as the number of exercise sessions attended versus prescribed. Adherence to the prescribed exercise dose will be calculated as the duration and intensity (aerobic component) or number of exercises, sets, repetitions, and weight (resistance component) completed vs prescribed. The supervising exercise professional will document the reason for each scheduled supervised exercise session that is not completed (i.e., clinical contraindication or self-selection) and for any modifications made to the prescribed aerobic or resistance exercise. For unsupervised home-based aerobic sessions (Phase 2), participants will be provided a hard copy aerobic based program, on which they will document the duration and intensity of their exercise completed. Research staff will then cross-check the returned programs with participants’ Fitabase data to determine the level of adherence to the prescribed duration and intensity. Adherence to the hourly unsupervised sedentary behaviour breaks will be automatically documented into Fitabase (Fitabase Small Steps Labs, LLC, San Diego, CA) upon syncing of each participant's Fitbit data, and calculated as the average number of hourly sedentary behaviour breaks completed per day versus prescribed.

### Data management

A unique study code will be assigned to all participants to ensure the confidentiality of their data is maintained. The secure online data management system REDCap (REDCap, Vanderbilt University, Nashville, USA) will be utilised to store all data and this will only be accessible to members of the study team. All data entered electronically will be double-checked for accuracy. Due to the low risks associated with the exercise components of the intervention, there will not be a formal data monitoring committee for this study. However, the study team will meet monthly to review study progress and data will be checked at regular intervals throughout the study.

### Sample size calculation

No prior studies have directly assessed the effect of a structured exercise intervention on changes in VO_2_peak and cardiac output in this patient cohort. As such, we based our sample size calculations on data collected from our group’s previously published work that utilised a similar exercise intervention in women being treated for breast cancer [74], whereby clinically meaningful changes in cardiorespiratory fitness and cardiac function were observed. The present study is powered to detect a minimum between-group difference in VO_2_peak of 10% (SD = 11%, effect size = 0.91) and cardiac output of 9% (SD = 10%, effect size = 0.9) after treatment, assuming a conservative correlation coefficient of *r* = 0.4 between baseline and follow-up testing. To detect this difference 20 completions per group are required (80% power; alpha = 0.025; multiple primary endpoints). To account for withdrawals, mortality associated with disease progression and treatment, and uncertainty related to the COVID-19 pandemic, a total of 60 participants will be recruited (Ex + SED; *n* = 30 and UC; *n* = 30).

### Statistical analyses

To examine the differential effects of the intervention on VO_2_peak, peak cardiac output, and additional secondary and exploratory outcome measures, generalised linear mixed modelling will be conducted (adjusted for baseline values) with participants as the random effect, time as the repeated measures factor, and group and group-by-time interactions as the fixed effects. The covariance structure of the model will be informed by the Akaike information criteria. The primary analysis will be conducted on an intention-to-treat basis and a probability level of 0.025 will be adopted to account for multiple primary outcome endpoints. Standardised effect sizes (Cohen’s *d*) will be calculated to determine the magnitude of change for within and between group effects. A per protocol analysis including participants who completed > 66% of the planned exercise sessions will also be performed.

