**Exploratory Outcomes**				
-Vascular function	CMR	✔		✔
-Cardiac mass	CMR	✔		✔
-Diffuse myocardial fibrosis	CMR	✔		✔
-Diastolic and systolic cardiac function	Echocardiography	✔	✔	✔
-Thigh muscle volume	Thigh MRI	✔		✔
-Thigh muscle fat fraction	Thigh MRI	✔		✔
-Oxygen uptake kinetics	CPET	✔		✔
-Body composition	DXA	✔	✔	✔
-Cardiovascular biomarkers	Blood Samples	✔	✔	✔
-Engraftment indices	Blood Samples	✔	✔	✔
-Development of acute GVHD	Blood Samples	✔	✔	✔
-Anxiety and depression	HADS	✔	✔	✔
-Dietary intake	Diet Diary	✔	✔	✔
-Habitual Physical Activity	Accelerometry/Fitabase	✔	✔	✔
-Habitual Sedentary Time	Inclinometry/Fitabase	✔	✔	✔
-Habitual Sleep Quality	Sleep Log/Fitabase	✔	✔	✔

Cardiopulmonary exercise test (*CPET*), cardiac magnetic resonance imaging (*CMR*), exercise cardiac magnetic resonance imaging (ExCMR), functional assessment of cancer therapy with bone marrow transplant (*FACT-BMT*) questionnaire, functional assessment of chronic illness therapy (*FACIT-fatigue*) questionnaire, dual energy x-ray absorptiometry (*DXA*), graft versus host disease (*GVHD*), Hospital anxiety and depression scale (*HADS*), cardiovascular disease biomarkers include HbA1c, fasting glucose, troponin-I, BNP, LDL- and HDL-cholesterol, triglycerides

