The primary outcomes for assessing the efficacy of the intervention on cardiovascular health will be change in VO_2_peak assessed via cardiopulmonary exercise testing and peak cardiac output assessed via exercise cardiac magnetic resonance imaging (ExCMR) (multiple primary outcomes). Secondary outcomes will include prevalence of functional independence (VO_2_peak ≥ 18 mL.kg^−1^.min^−1^) as well as patient reported fatigue and quality of life. Exploratory outcome measures will include changes in cardiac reserve, indices of resting cardiac structure and function (cardiac mass, myocardial fibrosis, diastolic and systolic function), central vascular compliance, cardiovascular biomarkers (troponin-I [cTn-I], brain natriuretic peptide [BNP], glycaemic control, lipid profile and adiposity), skeletal muscle structure and function (lean body mass, thigh muscle cross-sectional area and fat fraction, oxygen uptake kinetics, and muscular strength, power and stability) as well as anxiety, depression and transplant related outcomes including engraftment indices (time to neutrophil and platelet engraftment, immune reconstitution) and development of GVHD. The study will also assess habitual physical activity and dietary intake due to their potential impact on cardiovascular outcome measures. An overview of the protocol assessments and outcomes can be seen in Fig. 2.

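### The baseline-adjusted repeated-measures model set for all exploratory outcomes does not suit time to engraftment, and for GVHD its baseline term is empty and it describes status by visit rather than development

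*Protocol article*

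**What the plan says.** The protocol article's Statistical analyses section uses one sentence for every outcome. It names VO2peak, peak cardiac output and "additional secondary and exploratory outcome measures, generalised linear mixed modelling will be conducted (adjusted for baseline values"), and builds the model "with participants as the random effect, time as the repeated measures factor, and group and group-by-time interactions as the fixed effects". No outcome is exempted, and no time-to-event or competing-risk method appears anywhere in the article.

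The text after Table 3 in the Experimental protocol section lists among the exploratory outcomes "engraftment indices (time to neutrophil and platelet engraftment, immune reconstitution) and development of GVHD". Table 3 has rows for "Engraftment indices" and "Development of acute GVHD". Both give blood samples as the method and are ticked at baseline, post-inpatient and 12 weeks. Study design places baseline about two weeks before admission, so before the graft. The Transplant outcomes section names a different source, the medical records, for "time to engraftment, GVHD prophylaxis, development and severity, steroid use".

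Sample size calculation gives "mortality associated with disease progression and treatment" as one reason for recruiting 60 patients when 40 completers are needed. Participant withdrawals says that data already collected from patients who die are kept in the analysis.

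**The concern.** A model with a baseline covariate and a repeated time factor needs a pre-treatment value and more than one later value per patient. Time to engraftment has neither. GVHD from this graft can only be absent before the graft, so adjusting for its baseline does nothing. Both outcomes are events that death can prevent, and a visit-based model has no record for a patient who has died.

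These two outcomes bear on whether training during transplant affects the graft. There is no data monitoring committee (Data management). Adverse events are asked about before each training session in the exercise arm only, and deaths and hospitalisations from disease progression are not counted as adverse events (Adverse events). Engraftment and GVHD are therefore among the few transplant-related comparisons collected in the same way in both arms, so their analysis should match the type of outcome.

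**Working it through.** The plan gives no figure for these outcomes, so there is none to reproduce. The check is whether the stated fixed effects (intercept, group, time, group-by-time, baseline value) can be estimated from the data that each outcome supplies, with 30 patients per arm.

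**Time to engraftment.** There is one row per patient, 60 rows if all engraft.

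| Column | Content | Adds information? |
|---|---|---|
| Intercept | 1 for all | yes |
| Group | 0 or 1 | yes |
| Baseline | no value exists; entered as a constant | no |
| Time | one level, equal to the intercept | no |
| Group-by-time | equal to group | no |

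The rank is 2 of 5. Only a group contrast can be estimated. The participant random effect has no replication to support it. The contrast covers only patients who have an engraftment time; those who die first have none.

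**GVHD status at two post-baseline visits.** There are two rows per patient, 120 rows. Intercept, group, time (0 or 1) and group-by-time are independent. The baseline column is 'no' for everyone. The rank is 4 of 5 with baseline, and 4 of 4 without it. The model can therefore be fitted, for example with a logit link, once the baseline term is removed. It then estimates the odds of having GVHD at each visit, not its occurrence over follow-up.

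**Death before the event.** The documents give no rates, so the following are assumptions. Let c be the true cumulative incidence of GVHD and m the proportion who die without it. If those who die GVHD-free have no record, the observed proportion is c / (1 − m).

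- c = 40%, m = 10%: 0.40 / 0.90 = 44.4%
- c = 40%, m = 15%: 0.40 / 0.85 = 47.1%
- c = 40%, m = 20%: 0.40 / 0.80 = 50.0%
- Over c = 30–50% and m = 5–20%, the result runs from 0.30 / 0.95 = 31.6% to 0.50 / 0.80 = 62.5%.

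If c were 40% in both arms but m were 10% in one and 20% in the other, the apparent gap would be 50.0 − 44.4 = 5.6 points. The standard error of an arm difference at 40% is √(2 × 0.4 × 0.6 / 30) = 12.6 points. Complete exclusion is the extreme case, because a patient who dies after the post-inpatient visit still contributes that visit.

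**The case against.** A generalised linear mixed model accepts binary outcomes, so GVHD can be analysed under the stated sentence. A redundant baseline column is a wording defect that software would simply drop. Even for time to engraftment a group contrast survives. These outcomes are exploratory, the article condenses a fuller document, and the handling of competing deaths is commonly left to that document. Data collected before death are kept, and events come from medical records, so a GVHD event recorded before death is not lost. Engraftment indices also include immune reconstitution, which can be measured repeatedly in blood and can have a pre-transplant value, so the mixed model and the three visit ticks are reasonable for it.

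Most of this stands. A reader might infer that neither outcome can be analysed at all, but the rank check does not support that for GVHD. A reader might also infer that the plan drops or censors deaths; the article states neither rule, so the percentages above illustrate a risk and do not measure the plan. Nor does the lack of a competing-event rule count as an error on its own.

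The mismatch itself remains. The article does not leave these outcomes open: it assigns them a model with baseline adjustment and repeated time. An analysis plan that treated them properly would have to depart from that sentence, not merely add detail to it.

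**Conclusion.** The point holds in limited form. For time to neutrophil and platelet engraftment the stated model does not fit the outcome: three of its five fixed-effect columns carry no information, and death before engraftment leaves no value. For GVHD the model can be fitted, but its baseline adjustment is empty and it answers a question about status at visits rather than about development. The GVHD result rests on every patient being free of GVHD from this graft at baseline, which follows from the timing of that visit.

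The consequence is confined to exploratory outcomes. The size of any distortion from deaths cannot be computed from the article; under the assumed rates a between-arm gap of about 6 points is possible, roughly half a standard error at this sample size. It would be wrong to read this as a threat to the primary or secondary analyses or to the sample size, or to conclude that every Table 3 tick in these rows is mistaken.

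**What to change.** - In Statistical analyses, exempt time to neutrophil engraftment, time to platelet engraftment and development of GVHD from the mixed-model sentence.
- Analyse them from the day of transplant as cumulative incidence by arm, with death as a competing event. Compare arms by Gray's test or a cause-specific hazard model that accounts for the randomisation strata: conditioning intensity and, where numbers allow, sex. The two factors make four strata, or 60 / 4 = 15 patients each on average, so using both may be too fine.
- Keep repeated immune-reconstitution measures in the mixed model and keep their Table 3 visits.
- Reconcile the Table 3 baseline tick for acute GVHD, and for the time-to-engraftment part of the engraftment row, with Transplant outcomes, which takes both from medical records.

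The cost is a sentence or two in the analysis section and a correction to two table rows. The event data are already to be taken from medical records, so no new collection is planned beyond confirming that event dates are recorded. The downside is two or three extra exploratory analyses to program.

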**Primary Outcomes**				
-VO_2_peak	CPET	✔		✔
-Peak cardiac output	ExCMR	✔		✔

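### The repeated-measures model stated for the primary outcomes does not fit their single follow-up; at 20 completers per arm, power is about 61% to about 80% depending on how the model is run

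*Protocol article*

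**What the plan says.** Statistical analyses in the protocol article gives one model for primary, secondary and exploratory outcomes alike: "generalised linear mixed modelling will be conducted (adjusted for baseline values) with participants as the random effect, time as the repeated measures factor". Group and group-by-time are listed as the fixed effects. The section adds: "The covariance structure of the model will be informed by the Akaike information criteria". It sets 0.025 as the significance level for each primary outcome. It does not say whether baseline is also a response row, or which term tests the primary hypothesis.

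Table 3 (Experimental protocol) has three assessment columns. Under Primary Outcomes, VO2peak and "Peak cardiac output" are ticked at baseline and at 12 weeks only; the post-inpatient cell is empty for both. Quality of life and fatigue are ticked at all three visits.

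For the first primary outcome, Sample size calculation uses this target: "minimum between-group difference in VO_2_peak of 10% (SD = 11%, effect size = 0.91"). For the second it uses a difference of 9% with an SD of 10%, an effect size of 0.9. The link between the two visits enters through this phrase: "assuming a conservative correlation coefficient of *r* = 0.4 between baseline and follow-up testing". The section concludes: "To detect this difference 20 completions per group are required (80% power; alpha = 0.025; multiple primary endpoints"). Recruitment is 30 per arm, to allow for losses.

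**The concern.** The model suits outcomes with two post-baseline visits, such as the FACT-BMT and FACIT-Fatigue scores. The two primary outcomes have one.

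- **Baseline as covariate only.** Each participant contributes one response. Time has one level, group-by-time cannot be estimated, and a participant random effect cannot be separated from residual error.
- **Baseline as a response row.** Time has two levels and the interaction exists, but it is simply the between-arm difference in mean change. Adding baseline as a covariate as well puts the same measurement on both sides of the model and does not alter that estimate.

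These versions differ in power, and one of them can have the wrong error rate. The test of both primary hypotheses is therefore not uniquely fixed by the text, and the number of completers needed depends on which version is run.

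**Working it through.** **Inputs (Sample size calculation).** d = 10/11 = 0.909 for VO2peak and 9/10 = 0.90 for cardiac output; r = 0.4; n = 20 completers per arm; alpha 0.025. Assumed, because not stated: a two-sided test, and an SD that refers to a single time point with equal variances.

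**1. Reproducing the plan's 20 per arm.** With z = 2.2414 and 0.8416, (2.2414 + 0.8416)² = 9.505, and n per arm = 2 × 9.505 × V / d², where V is the variance factor.

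| Analysis | V | VO2peak | Cardiac output |
|---|---|---|---|
| ANCOVA | 1 − r² = 0.84 | 19.3 → 20 | 19.7 → 20 |
| 12-week value only | 1 | 23.0 → 24 | 23.5 → 24 |
| Change from baseline | 2(1 − r) = 1.2 | 27.6 → 28 | 28.2 → 29 |

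Of these, ANCOVA gives the stated 20 for both outcomes.

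**2. Power at 20 per arm.** The noncentrality is d / √(2V/20).

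- ANCOVA: 0.909 / √0.084 = 3.137 and 0.90 / √0.084 = 3.105. Power is 78.5% and 77.6% by noncentral t, or 81.5% and 80.6% by normal approximation.
- Group-by-time (change): 0.909 / √0.12 = 2.624 and 0.90 / √0.12 = 2.598. Power is 61.6% and 60.7% by noncentral t, or 64.9% and 63.9% by normal approximation.

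**3. Group-by-time with more completers (noncentral t).** At 25 per arm, power is 73.1% and 72.1%. At 30 per arm it is 81.7% and 80.8%. Reaching 80% takes 29 completers per arm for VO2peak and 30 for cardiac output, that is, nearly all of the 30 recruited.

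**4. Baseline as response and covariate, with a random intercept.** Take unit variances. The pooled slope on baseline is (1 + r)/2 = 0.7.

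- Residual covariance between a participant's two rows: −(1 − r)²/4 = −0.09. An intercept variance that cannot be negative is therefore estimated as zero.
- Average residual variance: (3 + r)(1 − r)/4 = 0.51. The model then treats the variance of a within-person difference as 2 × 0.51 = 1.02.
- The true value is 2(1 − r) = 1.2. The ratio is 1.02/1.2 = 0.85.
- Large-sample type I error: 2 × [1 − Φ(2.2414 × √0.85)] = 3.9%, against 2.5%.

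In 20,000 simulated trials with 20 per arm, the type I error was about 4.0% using t with 75 degrees of freedom and about 4.4% using the normal reference. The residual cross-product was negative or zero in every trial. Nominal power in this version is 67% to 71%, but only because the standard error is too small. A covariance structure that allows negative within-person correlation brings the error back to about 2.3% in simulation, which is close to nominal.

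**The case against.** The strongest reply is that baseline adjustment plus a single follow-up points to ANCOVA. The redundant terms drop out, the sample size agrees, and type I error is nominal. This is also a condensed article, and the layout of response rows and the exact contrast are often left to an SAP, which is not shown. Much of this stands: ANCOVA is the most natural reading, and under it the stated power is essentially right. But the article does more than omit detail. It states a model for the primary outcomes whose repeated factor, random effect and interaction cannot be estimated on that reading.

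Some stronger inferences are tempting but not supported:

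- **That the primary analysis has 61% power.** This needs baseline as a response row, the interaction as the primary test, and only 20 completers per arm. The article states neither of the first two, and 20 is the planning minimum out of 30 recruited.
- **That low power and inflated error occur together.** They belong to different versions. The change test with a valid standard error has nominal type I error. The inflation needs baseline on both sides and a non-negative random intercept.
- **That time is excluded as a fixed effect, so that the interaction would pick up any common decline.** The same sentence names time as the repeated factor. Listing only group and group-by-time beside it is probably shorthand.
- **That choosing the covariance by AIC should be dropped.** That sentence also covers outcomes with three visits, where the structure matters.
- **That 20 per arm can arise only from ANCOVA.** Sidedness is not stated. A 12-week-only comparison at one-sided 0.025 gives 19 and 20, although it makes no use of r.

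**Conclusion.** The point holds in this form: the stated model does not fit either primary outcome on the trial's own visit schedule, and the article does not identify the test. Depending on how the model is run, power at 20 completers per arm is about 61% (difference in change) to about 80% (ANCOVA). One further version, with baseline on both sides and a non-negative random intercept, has a type I error of about 4% against 2.5%. The range narrows in absolute terms if more participants complete; at 30 per arm even the change test reaches about 81%.

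The figures assume a two-sided 0.025 test, r = 0.4, and an SD for a single time point with equal variances at both visits. If the SD is instead that of change, r plays no part and power at 20 per arm is about 70%.

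**What to change.** In Statistical analyses, give the two primary outcomes their own sentence: the 12-week value is regressed on group, baseline value and the stratification factors (conditioning intensity and sex), and the group coefficient is tested at 0.025. An acceptable alternative is a constrained longitudinal model, with baseline as a response only and a common baseline mean in both arms.

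Keep the repeated-measures model, including its covariance selection, for outcomes with two follow-ups. For those, state that baseline enters as a covariate only, list time as a fixed effect, and name the 12-week group contrast as the test.

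The cost is wording: no new participants, visits or data, and the sample size of 20 completers per arm still matches its analysis. The change should be made before group comparisons are run.
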